## **MATERIALS & METHODS:**

**Trial design {8}:** It will be a parallel group, quadruple blind-randomized controlled pilot trial annexed with a laboratory based study.

**Study settings & duration {9}:** The clinical trial will be carried out at the Aga Khan University Hospital (AKUH), Karachi, Pakistan. The total duration of the study is expected to be 6 months i.e. August 2020-January 2021. The viral PCR tests will be done at main AKUH clinical laboratories whereas the immunological tests (cytokine analysis) will be done at the Juma research laboratory of AKUH. The study protocol is already registered at [www.clinicaltrials.gov](http://www.clinicaltrials.gov) with ID# NCT 04341688.

**Sampling technique & Eligibility criteria {10}:** Non probability, purposive sampling technique will be followed to identify a total of 50 participants for this study. The inclusion criteria are laboratory confirmed COVID-19 positive males or females (in the age range of 18-65 years), with mild to moderate disease, already admitted in the AKUH. Subjects who have more than 7 days of the onset of COVID-19 symptoms, edentulous patients, subjects with low Glasgow coma score, intubated patients, history of radiotherapy or chemotherapy will be excluded. Patients who are being treated with any form of oral or parenteral antiviral therapy will be excluded. Patients with known pre-existing chronic mucosal lesions such as lichen planus will also be excluded. Patients who are allergic to the study drugs (Povidone-Iodine, Hydrogen Peroxide, Neem Extract or Hypertonic Saline) will also be excluded.

**Intervention {11a}:** Group A (n=10) patients on 10 ml gargle and nasal lavage using 0.2% Povidone-Iodine (Betadiene® by Aviro Health Inc./ Pyodine® by Brooks Pharma Inc.) for 20-30 seconds, thrice daily for 6 days. Group B (n=10) patients will be subjected to 10 ml gargle and nasal lavage using 1% Hydrogen peroxide (HP® by Karachi Chemicals Products Inc./ ActiveOxy® by Boumatic Inc.) for 20-30 seconds, thrice daily for 6 days. Group C will comprised of (n=10) subjects on 10ml gargle and nasal lavage using Neem extract solution (*Azardirachta indica*)

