formulated by Karachi University (chemistry department laboratories) for 20-30 seconds, thrice daily for 6 days. Group D (n=10) patients will use 2% hypertonic saline (Plabottle® by Otsuka Inc.) gargle and nasal lavage for a similar time period. Group E (n=10) will serve as positive controls. These will be given simple distilled water gargles and nasal lavage for 20-30 seconds, thrice daily for six days. For nasal lavage, a special douche syringe will be provided to each participant. Its use will be thoroughly explained by the data collection officer. After each use, patient is not supposed to eat, drink or mouth rinse for next 30 minutes.

**Discontinuation of intervention {11b}:** Patients who develop rashes, or any other mucosal reaction in oral mucosa or patients who do not wish to continue with the gargles and nasal lavage will be discontinued in the study.

**Compliance on intervention {11c}:** The data collection officer will monitor the amount of gargling solution consumed on daily basis to record the patient compliance on intervention. And once the study is over, the residual bottle will be collected and sent to the incineration. Similarly, any unused/ partially used study drug bottle will be destroyed via incineration.

**Concomitant care {11d}:** Study participants will continue to get their needed routine inpatient medical/pulmonology care concomitantly as per the individual requirements under the care of the attending physician(s).

**Outcomes {12}:** Primary outcome is the reduction in the intra-oral viral load confirmed with real time PCR. Secondary outcome is the change in inflammatory biomarkers (IL-2, IL-4, IL-6, IL-10, TNF- $\alpha$ , IFN- $\gamma$  and IL-17) profiles in the five study groups.

**Participants' timeline {13}:** The timeline has been added as a flow diagram at the end of the protocol. Please see figure 1 on page no. 15.

**Sample Size {14}:** As there is no prior work on this research question, so no assumptions for the sample size calculation could be made. The present study will serve as a pilot trial. We intend to study 50 patients in five study groups. For details, please refer to figure 1 on page no. 15.

**Recruitment {15}:** Patients who are laboratory confirmed COVID-19 within 7 days of the onset of their symptoms who are already admitted as inpatient at the Aga Khan University Hospital, Karachi, Pakistan will be contacted for a voluntarily participation in the study.

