**Group allocation/ Randomization {16a}:** The assignment to the study group/ allocation will be done using sealed envelope method under the supervision of Clinical Trial Unit (CTU) of Aga Khan University, Karachi, Pakistan. The patients will be randomized to their respective study group immediately after the eligibility assessment and consent administration is done.

**Allocation concealment {16b}:** All the study drugs will be kept in identical dark colored bottles so that the intervention is masked.

**Implementation {16c}:** The Neem extract (*Azadirachta indica*) will be compounded at the Chemistry department, University of Karachi, Pakistan. This will be arranged from there whereas other drugs are stored at AKUH pharmacy/ distribution department. The CTU will ensure that only labels mentioning A, B, C, D or E are pasted on the bottles.

**Blinding/ masking {17a}:** Study will be blinded in quadruple. Patients, intervention provider, outcome assessor and the data collection officer will be blinded. The groups will be labelled as A, B, C, D or E. The codes of the intervention will be kept in lock & key at the CTU and will only be revealed at the end of study or if the study is terminated prematurely.

**Un-blinding {17b}:** Although, un-blinding is not permissible, however, if a participant recognizes the intervention using his/her prior knowledge or experience; they will still be encouraged to continue with the study drug till the end of the study. But if any patients develops a serious reaction to the intervention drug, then un-blinding will be done. The principal investigator will consult CTU and with their permission and taking primary attending physician onboard, un-blinding for the patient in question will be done. This will be documented on the proforma.

**Specimen collection {18a}:** The baseline oral swab will obtained (by a trained data collection officer using the required PPEs) from the posterior pharyngeal wall/ tonsillar area of the study participant on day one before initiating the gargles. Study participants will continue to use the

gargle and nasal lavage for 6 days. The end-point oral-pharyngeal swab will be taken on the day 7. Participants will be provided with a protective hood so that they themselves don't generate aerosols in the immediate vicinity while carrying out the gargling and nasal lavage. For nasal lavage, they will use the special douche syringe as described earlier.

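### The bottle and group letters A to E are the same letters that section 11a ties to named agents, so as written the code locked at the CTU does not protect the blind of staff who see a bottle and know the protocol.

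*Protocol*

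**What the plan says.** The relevant text is all under Materials & Methods in the protocol.

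Intervention {11a} gives each group a letter and an agent:
- "Group A (n=10) patients on 10 ml gargle and nasal lavage using 0.2% Povidone-Iodine"
- "Group B (n=10) patients will be subjected to 10 ml gargle and nasal lavage using 1% Hydrogen peroxide"
- "Group C will comprised of (n=10) subjects on 10ml gargle and nasal lavage using Neem extract solution"
- "Group D (n=10) patients will use 2% hypertonic saline"
- "Group E (n=10) will serve as positive controls. These will be given simple distilled water gargles and nasal lavage"

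Implementation {16c} sets the labelling rule: "The CTU will ensure that only labels mentioning A, B, C, D or E are pasted on the bottles".

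Blinding/masking {17a} lists who is masked: "Patients, intervention provider, outcome assessor and the data collection officer will be blinded". It continues: "The groups will be labelled as A, B, C, D or E". The same section says the intervention codes are held securely at the CTU and opened only when the study ends or is stopped early.

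Allocation concealment {16b} adds that the bottles look alike and are dark. Un-blinding {17b} allows the code to be opened for an individual patient after a serious reaction, with the CTU's permission.

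**The concern.** A locked code protects a blind only if the label on the bottle cannot be translated without it. Here the translation appears to be printed in section 11a. Bottles that look alike do not help when the letter on the bottle can be looked up.

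The role most exposed touches the trial at many points. The data collection officer teaches the use of the lavage syringe (11a), checks daily how much solution has been used (11c) and takes the baseline pharyngeal swab (18a). The same officer keeps in touch with discharged patients so that they continue and return on day 7 (18b), enters and codes the data (19), and explains the study at consent (26). The intervention provider can also be expected to handle labelled bottles.

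The Hypotheses section names povidone-iodine as more effective than hydrogen peroxide and hypertonic saline, so staff who know the arm have a stated expectation about the result. Coaching, encouragement to continue and swab technique are the routes by which that knowledge could act. What is at stake is whether the trial can be reported as quadruple blind, as its title says. A broken blind cannot be restored once patients have been enrolled.

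**Working it through.** No sample size, power or error-rate figure is involved. The check compares the sections and then counts patients per letter.

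**Step 1. Compare the letters.**

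| Letter | Agent in 11a | On bottles (16c) | Group label (17a) |
|---|---|---|---|
| A | 0.2% povidone-iodine | yes | yes |
| B | 1% hydrogen peroxide | yes | yes |
| C | Neem extract | yes | yes |
| D | 2% hypertonic saline | yes | yes |
| E | distilled water | yes | yes |

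All five letters match. Sections 11a and 17a also use the same noun, groups.

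**Step 2. Look for a second mapping.** Sections 16a, 16b, 16c, 17a and 17b do not say that the bottle letters are permuted relative to 11a. They do not mention kit or participant numbers on bottles either. The locked codes in 17a are not described further.

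**Step 3. Work through the two possible readings.**
- *The bottle letter is the 11a letter.* The code held at the CTU is the list in 11a. Seeing a letter and knowing 11a is enough to name the agent.
- *The CTU holds a separate, scrambled key.* The letter alone then reveals nothing. But the protocol does not say this, and staff following 16c literally would put A on povidone-iodine.

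**Step 4. Ask who meets both conditions (sees the letter, knows 11a).**
- Data collection officer: handles the bottles daily (11c) and explains the study to patients (26). Both conditions are plausible.
- Intervention provider: plausible on the same grounds, though the duties are not spelled out.
- Patients: see the bottle, but nothing says they receive the protocol.
- Laboratory outcome assessor: works on swabs delivered in transport medium (33). Nothing says a bottle or its letter reaches the laboratory.

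**Step 5. Count what one un-blinding reveals.** The plan has 50 patients in 5 groups, so 50 / 5 = 10 patients share each letter. Un-blinding one patient under 17b links that letter to an agent. The other 10 − 1 = 9 patients in the arm are then identified to anyone who learns the result and knows their letters. This holds under both readings in Step 3. With five secret symbols in place of the letters the count is still 9. With participant-level numbers it is 0.

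**The case against.** The best defence is that the protocol never states outright that the bottle letter equals the 11a letter. Locking up a code makes sense only if there is something to hide, so 17a can be read as implying a separate key, with the 11a letters serving as description. That reading is possible, and it makes the identity of the letters an inference. It does not remove the problem: no such key is described, the wording points the other way, and the one-letter-per-arm weakness remains in either case.

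Second, a reader might infer that the label un-blinds every role on the 17a list, or all 50 patients with certainty. The document does not support that. Disclosure needs both sight of the letter and knowledge of 11a, and neither the patients nor the laboratory assessor is shown to have both. Nor can it be said that the key is public. The protocol says the trial is registered, but not that the registry entry prints the letters beside the agents.

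Third, the room for bias is limited. The primary outcome is quantitative PCR read against a standard curve, and discontinuation under 11b follows a reaction or the patient's own wish. Section 17b also foresees that some participants will recognise their product, so the label's added contribution is unknown. These points stand as limits on how much harm can be claimed. They do not answer the defect, because swab collection, coaching and follow-up come before the assay and involve a person who is meant to be blinded.

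**Conclusion.** The point holds in a limited form. As written, sections 11a, 16c and 17a together allow anyone who sees a bottle and knows the protocol to name the agent. That plausibly covers two of the four roles listed as blinded: the data collection officer and the intervention provider. For them the code locked at the CTU gives no protection. Separately, un-blinding one patient exposes up to 9 others in the same arm, whichever reading of the letters is right.

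The first conclusion assumes that the bottle letters are the 11a letters, which is the natural but not the explicit reading, and that these staff know the content of 11a. The second assumes only one letter per arm and the planned 10 patients per group.

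It is tempting to turn this into a shift in log10 viral load. That would need a figure for how far knowledge of the arm changes swab recovery, and the document gives none. The size of the bias is unknown and should be reported as such. The labelling rule still needs correcting before any bottle is labelled, because following it literally compromises a blind that the trial's title claims.

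**What to change.** In sections 16c and 17a, replace the five letters with participant-level bottle numbers that the CTU generates and that bear no relation to the 11a letters. The CTU alone should hold the list linking each number to an agent. Add a sentence saying that the 11a letters are for description only and do not appear on any bottle, form or data file before the code is opened.

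A lesser change, five new secret symbols in place of A to E, would remove the link to 11a. It would leave one symbol per arm, so a single un-blinding would still reveal the whole arm. Participant-level numbers solve both problems.

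The cost is different printed labels, one CTU list and about a paragraph of protocol text. The number of patients, the outcomes and the analysis do not change.

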**Retention of study participants {18b}:** To retain maximum number of patients in the study, the data collection officer will keep the contact number of all the recruited patients, so that even if they are discharged from the hospital, they will be encouraged to continue with the study protocol and present to us on the day 7 at the AKUH dedicated COVID-19 testing facility for the collection of their endpoint pharyngeal swabs.

**Data management {19}:** A trained data collection officer will be responsible for data entry, coding, security, and storage. To ensure data quality, double data entry will be followed. The data collection officer will ensure coordination with the investigators and the statistician.

The period of retention of the data will be according to the CTU policy on this subject i.e. 15 years after the completion of the trial. The biological samples (pharyngeal swabs), and the partially consumed study drug will be discarded via incineration immediately after the data collection.

**Data Analysis {20}:** Data will be analyzed using SPSS for Windows (version 23.0 SPSS) and Graph Pad Prism 7.0 software.

Mean and standard deviation of the continuous variables (age, COVID-19 viral counts and cytokine profiles at baseline and endpoint etc.) will be computed. Frequency distribution of the categorical variables will be determined (gender, co-morbidities, presence of hypertension, diabetes, periodontal status etc.) Repeated measures ANOVA will be used to compare the reduction in intra-oral viral load and the changes in the inflammatory biomarkers in the study groups. In case of substantially low count of participants in the study groups, non-parametric tests such as Kruskal-Wallis or Friedman test will be employed. Generalized Estimation Equation (GEE) will be done to predict changes in the COVID-19 viral load and cytokine profiles. A subset analysis using Zero inflated negative binomial (ZINB) model will be employed, provided a

significant reduction in viral load is observed in any of the study groups. A p-value of  $<0.05$  will be taken as statistically significant. {20a}

The **biases and confounders** can be taken care at following four levels:

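### Section {17a} leaves the statistician outside the blind and opens the code at study end, the A–E letters are decoded in the protocol, and section {20} does not say which test of viral load decides

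*Protocol*

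**What the plan says.** **Who is blinded and until when.** Blinding/masking {17a} states: "Patients, intervention provider, outcome assessor and the data collection officer will be blinded". The codes are kept locked at the clinical trial unit and "will only be revealed at the end of study or if the study is terminated prematurely". Data management {19} mentions the analyst as a further role: "The data collection officer will ensure coordination with the investigators and the statistician". No blinding status is given for that role.

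**The letters.** Implementation {16c} says: "The CTU will ensure that only labels mentioning A, B, C, D or E are pasted on the bottles". Section {17a} labels the groups with the same five letters. Intervention {11a} begins "Group A (n=10) patients on 10 ml gargle and nasal lavage using 0.2% Povidone-Iodine" and goes on to assign hydrogen peroxide to B, Neem extract to C, hypertonic saline to D and distilled water to E.

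**The analysis.** Outcomes {12} states: "Primary outcome is the reduction in the intra-oral viral load confirmed with real time PCR". The scale (log or raw copies) is not given. Data Analysis {20} names repeated measures ANOVA for the comparison of groups and then says: "In case of substantially low count of participants in the study groups, non-parametric tests such as Kruskal-Wallis or Friedman test will be employed". It continues: "Generalized Estimation Equation (GEE) will be done to predict changes in the COVID-19 viral load and cytokine profiles". A zero-inflated negative binomial model follows as a subset analysis if any group shows a significant reduction. One threshold, p<0.05, covers everything. The paragraph on biases and confounders gives GEE the task of handling confounding and names no covariates.

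**The concern.** There are two separate weaknesses.

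The first is the blind at the analysis stage. The list of blinded roles reads as complete and omits the person who runs the tests. The release point for the code does not require that the data be locked or the primary analysis finished. Under {17a} as written, the agents could be known while decisions on scale, covariates, exclusions or the fallback test are still open. Even if the code stays locked, the letters may give the allocation away to anyone who has read {11a}.

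The second is the choice of test. Two analyses of the primary outcome are planned without condition, and a third replaces the first under a trigger that has no number. Planned arms are only 10, so the low-count clause could be argued either way in any realistic outcome of recruitment. If ANOVA and GEE disagree, the protocol does not say which one the conclusion rests on.

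**Working it through.** **Step 1: the plan's own figure.** The protocol gives no power calculation. The only figure to reproduce is 5 arms × 10 = 50 patients, which agrees.

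**Step 2: the texts on blinding side by side.**
- {17a} blinds four roles; {19} shows that a statistician exists; the two lists do not overlap.
- {17a} sets code release at study end or early termination; no section places database lock or a primary analysis before it.
- {11a} maps A–E to agents; {16c} and {17a} use A–E on bottles and groups. The protocol does not say that the letters on bottles are scrambled relative to {11a}. If they match, the key is already printed.

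**Step 3: size of the test multiplicity.** Inputs from the protocol: five arms, 10 each, two time points, threshold 0.05. Assumptions not in the protocol: log10 load SD 1.5, baseline–endpoint correlation 0.5, means 5 and 3 log10, no true difference between arms. Variants: 8 per arm, and endpoint values below 2 log10 set to zero (floor).

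Tests on change d = endpoint − baseline:
- With two time points, the group-by-time F test of repeated measures ANOVA equals one-way ANOVA on d.
- Kruskal-Wallis on d.
- GEE robust Wald test: W = (Cm)ᵀ(CVCᵀ)⁻¹(Cm), where m holds the five arm means of d, V is diagonal with entries s²/n (s² computed with divisor n), C holds the four contrasts, and W is referred to chi-squared on 4 df with no small-sample correction.

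Rejection rates under the null, 6,000 runs per row:

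| Setting | F | Kruskal-Wallis | GEE | F or K-W | Any of three |
|---|---|---|---|---|---|
| 10 per arm, log | 5.4% | 4.5% | 14.5% | 6.1% | 14.7% |
| 10 per arm, log, floor | 5.0% | 4.5% | 14.8% | 5.8% | 15.0% |
| 8 per arm, log | 5.6% | 4.5% | 17.2% | 6.3% | 17.2% |
| 8 per arm, log, floor | 4.7% | 3.6% | 16.6% | 5.2% | 16.6% |
| 10 per arm, raw | 1.1% | 4.6% | 7.5% | 5.5% | 11.6% |

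Simulation error is about √(0.05 × 0.95 / 6,000) = 0.3 percentage points at a rate of 5%.

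Allowing either scale, 10 per arm: F or Kruskal-Wallis on log or raw change gives 9.5% (10,000 runs) and 9.7–10.4% (6,000 runs for each of two mean settings). Adding GEE gives 16.8% and 17.2–18.1%.

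**Step 4: where the rise comes from.** In the first row, adding Kruskal-Wallis to F costs 6.1 − 5.4 = 0.7 points. GEE alone is at 14.5%, so counting all three adds only 14.7 − 14.5 = 0.2 points to it. The GEE excess is small-sample error: with 10 per arm the uncorrected variance is (10 − 1)/10 = 0.9 of the unbiased one, and chi-squared is used as if variances were known. For reference, independent tests at 0.05 would give 1 − 0.95² = 9.75% for two and 1 − 0.95³ = 14.3% for three.

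**Step 5: what the figures do not depend on.** All three are joint comparisons of five arms. Relabelling the arms leaves each p-value unchanged, so the rates are the same whether or not the analyst knows the agents. On the log scale without a floor, change is normal for any SD and correlation and the tests ignore its scale, so those rows depend only on normality and arm size. The raw and mixed-scale figures do depend on the assumed SD.

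**The case against.** The strongest reply is that most of this belongs in a statistical analysis plan, which is not at hand. Ranking of tests, outcome scale, covariates and the timing of lock are commonly settled there, and this is a 50-patient pilot with no power claim. That stands for scale and covariates taken alone. It does not remove the point, because the list of blinded roles, the release rule, the decoded letters and the overlapping tests with an unquantified switch are things that the protocol itself states. A later plan that named one test would not change {17a}.

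A second reply is that the tests are not four equal routes. This is right. ANOVA is the named comparison of groups, the non-parametric tests are a fallback, GEE is the adjusted analysis, and the zero-inflated model is a conditional subset analysis. The hierarchy is loose, not absent. What is missing is a statement of which result carries the conclusion and a number for the fallback.

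A reader might infer more: that the test can be picked knowing which agent it favours, and that, since the Hypotheses expect povidone-iodine to beat peroxide and saline, the bias runs in a known direction. The documents do not support this. They do not say that the statistician is unblinded, only that the role is not protected. The end of the study may include the analysis. The simulated rates do not change when arms are relabelled, so they are no evidence about unblinding or direction; blinding the statistician would leave them where they are.

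**Conclusion.** The point holds in two parts, to be kept apart.

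1. As written, {17a} does not secure a blinded analysis: the statistician is outside the list, the release of the code is not tied to lock or a finished primary analysis, and the A–E letters may already be decoded by {11a}. No size can be put on this, and no bias is shown.
2. Section {20} does not say which of ANOVA and GEE decides on viral load, and its fallback has no threshold. With 10 per arm, the chance of at least one false positive is about 5–6% for ANOVA or Kruskal-Wallis on log change, about 10% with log and raw scales mixed, and about 14–18% when uncorrected GEE also counts. Most of the last step is GEE's own small-sample error, which would remain if uncorrected GEE were the single prespecified test. A GEE with a small-sample correction would give a smaller rise.

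This is worth correcting because it costs almost nothing. It is not a fault that invalidates the trial.

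**What to change.** In {17a}: add the statistician to the blinded roles, and state that the clinical trial unit releases the key only after database lock and a signed primary analysis. Run that analysis on codes that differ from the A–E letters in {11a}.

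In {20}: name one between-group test on log10 copies as the sole basis for the primary conclusion, and label GEE and the other tests as sensitivity analyses. If a fallback is kept as part of that rule, give its trigger as a number. Friedman's test should not serve as the fallback for the group comparison, since it is a within-subject test and does not compare parallel groups.

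Cost: a few sentences, one set of neutral codes, and a slightly later release of the key, which the trial unit already holds.

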**Informed consent {32}:** Informed consent will be obtained in Urdu (or in English for those who are well versed with the latter) language where the harms and benefits of the gargles and nasal lavage will be explained along with the method of their use in a simple language. The details are stated in the Urdu and English consent forms. The signed consent forms will be retained for the record purpose.

**Laboratory phase for Biological specimen {33}:** Swabs taken from the posterior pharyngeal wall and tonsillar area will be delivered to the laboratory in the transport medium within 4 hours of the specimen collection. The RNA will be extracted in the biosafety cabinet in the BSL-3 laboratory using QIAamp Viral RNA Mini Kit (Qiagen Inc.). Viral RNA will be used as a template in PCR containing following two sets of CDC approved primers and probes targeting COVID-19 virus and Fast Virus 1-Step Master Mix (Thermofisher Inc.). 2019-nCoV\_NI-F (GACCCCAAAATCAGCGAAAT), 2019-nCoV\_NI-R (TCTGGTTACTGCCAGTTGA ATCTG), 2019-nCoV\_NI-P (FAM-ACCCCGCATTACGTTTGGTGGACC-BHQ1) 2019-nCoV\_N2-F (TTACAAACATTGGCCGCAAA) 2019-nCoV\_N2-R (GCGCGACATTCCGAAGAA), 2019-nCoV\_N2-P FAM-(ACAATTTGCCCCCAGCGCTTCAG-BHQ1). To generate standard curve, we will design a synthetic oligo which will contain target sites for the aforementioned forward & reverse primers and probes. We will clone this synthetic oilgo in pGEMT vector after amplifying it through PCR; calculate its copy numbers and use its different dilutions to generate the standard-curve in PCR. Sample Ct values below 35 cycles will be considered as positive. The unknown sample's Ct values will be plotted on standard curve to know the copy numbers.

Cytokine analyses from the collected specimen will be carried out using Cytometric Bead Array (BD Biosciences) on FACS Celesta analyzer. Cytokine bead array detects cytokines using fluorescence labelled beads coated with antibodies. Following incubation of samples with cytokines, a fluorescence labelled antibody is used for the signal detection. The Median Fluorescence Intensity (MFI) is proportional to the amount of analyte present in the sample. All

procedure will be carried as per manufacturer's instructions. Unknown concentration of cytokines will be quantified through a known standards curve of cytokines. Flow JO software will be used for the final analyses.

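### Read plainly, the primary analysis is an ANOVA on change in untransformed copy numbers, which would very likely miss even a 100-fold effect in one arm.

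*Protocol*

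**What the plan says.** Outcomes {12} gives the primary outcome without a scale: "Primary outcome is the reduction in the intra-oral viral load confirmed with real time PCR". The laboratory section {33} fixes the unit: "The unknown sample's Ct values will be plotted on standard curve to know the copy numbers". It also sets a cut-off, "Sample Ct values below 35 cycles will be considered as positive", but assigns no value to results at or above it.

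Data Analysis {20} then names four procedures for viral load:

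- Summary and main test: "Mean and standard deviation of the continuous variables (age, COVID-19 viral counts and cytokine profiles at baseline and endpoint etc.) will be computed", and "Repeated measures ANOVA will be used to compare the reduction in intra-oral viral load".
- Fallback: "In case of substantially low count of participants in the study groups, non-parametric tests such as Kruskal-Wallis or Friedman test will be employed". The threshold is not defined, and the variable to be ranked is not named.
- Regression: "Generalized Estimation Equation (GEE) will be done to predict changes in the COVID-19 viral load and cytokine profiles", with no scale, family or link.
- A conditional step: "A subset analysis using Zero inflated negative binomial (ZINB) model will be employed, provided a" significant fall in viral load has first been seen in some arm.

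Swabs are taken on day 1 before gargling and on day 7 (Specimen collection {18a}). There are five groups of 10 (Intervention {11a}). The significance level is 0.05, and section {20c} adopts intention to treat. The only viral result given in log10 units is that of the hypertonic saline trial cited in the Rationale {6b}.

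**The concern.** Copy numbers from a PCR standard curve can span several orders of magnitude. On that scale an arithmetic mean and SD describe the one or two highest values rather than the arm. Subtracting day 7 from baseline makes matters worse, because once the load has fallen tenfold or more the difference is nearly the baseline itself, and the depth of the fall disappears.

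This is the sole primary outcome, and the protocol states efficacy hypotheses and tests them at p<0.05. If the wording is followed, the arms will be ranked mostly by who entered with the highest swab, and a null result will say almost nothing about the gargles. The means and SDs would also be a poor basis for sizing a later trial, which is a main product of a pilot.

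**Working it through.** **There is no stated figure to reproduce.** Sample Size {14} says that no assumptions could be made, so SD, effect and power are absent. Everything below marked as assumed is mine.

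**Inputs from the protocol:** 5 arms of 10, two time points, alpha 0.05, outcome in copy numbers.

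**Assumed:** log10 copies normally distributed with SD 1.0, 1.5 or 2.0; baseline mean 6; control fall 2 log10; baseline/day-7 correlation 0.3; one arm with an extra fall of 2 log10 (100-fold).

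**Step 1: what the test compares.** With two time points, the group-by-time test of a repeated measures ANOVA equals a one-way ANOVA on change, with 5 − 1 = 4 and 50 − 5 = 45 degrees of freedom.

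**Step 2: what raw change measures.** Take a baseline of 10^8.

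- Fall to 10^5: 100,000,000 − 100,000 = 99,900,000.
- Fall to 10^3: 100,000,000 − 1,000 = 99,999,000.

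The second patient ends 100 times lower, yet the two reductions differ by 99,000, about 0.1%. On the log10 scale the falls are 3 and 5.

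**Step 3: power by simulation** (4,000 trials per setting, 2,000 for the rank tests; no censoring).

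| Analysis | SD 1.0 | SD 1.5 | SD 2.0 |
|---|---|---|---|
| ANOVA on raw change | 1.8% | 1.2% | 0.6% |
| Same test, no true effect | 1.6% | 1.2% | 0.6% |
| Kruskal-Wallis on raw reduction | 4–6% | 4–6% | 4–6% |
| Kruskal-Wallis on day-7 counts | 99% | 78% | about 50% |
| ANOVA on log10 change | 97% | 67% | 41% |
| Day-7 log10, baseline-adjusted | 99.8% | 86% | 59% |

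The first two rows are practically equal: the raw test rejects about as often with a 100-fold effect as with none.

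**Step 4: why.** The highest patient supplies a median 55%, 71% and 82% of an arm's raw mean at SD 1.0, 1.5 and 2.0. The largest single value carries a median 63–66%, 79–82% and 88–90% of the raw-change sum of squares.

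**Step 5: sensitivity to the assumptions** (correlation 0.3 or 0.6, effect in one or in all four active arms).

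- SD 1.0 to 2.0, control fall 0.5 to 2 log10: raw power about 2% down to 0.6%. Kruskal-Wallis on raw reduction: 4–15%.
- SD 0.5 to 0.75, same falls: raw power 2–6%.
- SD 0.3, control fall 0.5: 12–13%.
- No control fall: 70–87% at SD 0.3, 18–32% at SD 0.5, 6–11% at SD 0.75.

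**Step 6: the cut-off.** The copy number at Ct 35 is not in the protocol. In this scenario the effective arm has a day-7 mean of 6 − 2 − 2 = 2 log10. At SD 1.5, half of that arm lies below a floor of 2, and Φ((3 − 2)/1.5) = Φ(0.67), about 75%, below a floor of 3. With values below the floor set to it, baseline-adjusted log10 power falls from 86% to about 75% (floor 2), 68% (floor 2.5) and 53–55% (floor 3). Log10 change falls from about 67% to 44%, 34% and 22%. A Tobit model was not simulated.

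**The case against.** **The raw scale is inferred.** The protocol never says untransformed, and a statistical analysis plan that is not shown could set a log scale. A reader should not claim that raw analysis is explicitly declared. What stands against this defence is that the protocol does more than stay silent. It fixes the summary (mean and SD of counts), the unit (copies) and the test (ANOVA on the reduction). A later plan that followed it would inherit the problem.

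**Other methods are named.** A reader might infer that every planned analysis is on the raw scale. That goes too far. The count part of a zero-inflated negative binomial normally has a log link, so it gives fold differences; its weaknesses are that it runs only after significance and that it suggests non-detects are zeros. GEE could be fitted on a log scale, but no scale or link is stated. Kruskal-Wallis would perform well on day-7 counts, and with 10 per arm the fallback might be invoked. But its trigger is a low number of participants rather than skewness, and the only variable the section names for comparison is the reduction, where ranks do not help.

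**The spread is assumed.** A reader might infer that the effect is certain to be missed. The protocol gives no SD, and with SD near 0.3 log10 and no natural decline the raw test does work. So very likely missed is as far as this goes.

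**It is a pilot.** There is no power target to fail. That is true, but the protocol still tests efficacy hypotheses at 0.05.

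**Conclusion.** The point holds on the plain reading of Data Analysis {20} with the laboratory section {33}. The primary comparison as worded is nearly uninformative: about 2% power or less for a 100-fold effect in one arm, at log10 SD 1.0 to 2.0, control fall 2 log10 and correlation 0.3. The result is stable for SD 0.5 to 2.0 whenever controls fall by at least 0.5 log10 (6% at most).

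The gain from a log10, baseline-adjusted analysis is large but should not be quoted free of censoring. At SD 1.5 it is about 86% with every value observed, and about 55–75% with floors of 2 to 3 log10 copies, both floors being assumptions.

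A reader might also conclude that patients whose baseline swab is Ct 35 or more should leave the primary comparison, since they cannot show a fall. The documents do not support that as the primary analysis: it departs from the intention-to-treat statement in {20c} and would shrink arms of 10 by an unknown number.

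**What to change.** In Outcomes {12} and Data Analysis {20}:

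1. Define the primary outcome as log10 copies at day 7, compared between arms with adjustment for baseline log10 copies, in all randomised patients.
2. Report geometric means and fold differences with confidence intervals in place of arithmetic means and SDs of counts.
3. State that Ct 35 or more is left-censored at the copy number corresponding to Ct 35 on the standard curve, for example in a Tobit model, and is not a zero count.
4. If a rank test is kept, name its variable as day-7 counts or log10 change, never raw reduction, and define when it is used.
5. State the scale and link for the GEE, and analyse cytokines on the log scale.
6. Use restriction to baseline Ct below 35 only as a sensitivity analysis.

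The cost is analysis wording: no extra patients, visits or assays. The small downside is that results are read as fold changes rather than differences in copies.
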